#### Footnotes

a Subjects who prematurely discontinue all study medication (PegIFN $\alpha$ -2a/RBV) should switch to the visit schedule as laid out in Time and Events Schedule - Part 4 (unless the subject withdraws consent).

b Free thyroxine (T4) and free triiodothyronine (T3) will be assessed if TSH is abnormal.

- c The biochemistry sample at Weeks 24, 36, and 48 must be taken after fasting for at least 10 hours. It is recommended that biochemistry samples at all other time points also be taken after fasting for at least 10h. The homeostasis model assessment for insulin resistance (HOMA IR) index will be derived from insulin and glucose (fasted) test results at Weeks 24, 36, and 48.
- d Urinalysis performed locally by dipstick. If there are clinically relevant abnormalities in the investigator's opinion, further urinalysis should be done locally (e.g., sediment analysis including RBC, WBC, casts). Clinically relevant findings from local urinalysis will be reported as AEs.
- e Urine test for women of childbearing potential. Extra pregnancy test kits will be given if more than 4 weeks between two consecutive study visits to perform a pregnancy test at home.
- f Sequencing of the HCV NS3/4A region will be done at the discretion of the Study Responsible Scientist.
- g Non-invasive confirmation of the liver condition (by transient elastography). All effort should be made to use the same assessment method as used to assess fibrosis stage at inclusion.
- h PRO scales should be completed prior to any other study-related activity at each visit.
- i From signing the ICF until 4 weeks after last study medication intake. Thereafter, only AEs considered related to TMC435 will be reported. SAEs will be reported until 30 days after last study-related procedure.

# TIME AND EVENTS SCHEDULE - PART 4: IN CASE OF PREMATURE DISCONTINUATION OF ALL STUDY MEDICATION (TMC435/PEGIFN $\alpha$ -2A/RBV DURING THE FIRST 12 WEEKS OR PEGIFN $\alpha$ -2A/RBV AFTER WEEK 12)

| Visit Type
Study Week                                                                             | Early Withdrawal Visit                                         | Follow-up after early withdrawal a |                                                                                     |
|------------------------------------------------------------------------------------------------------|----------------------------------------------------------------|-----------------------------------------------|-------------------------------------------------------------------------------------|
|                                                                                                      | At time of
early discontinuation of
all study medication | 4 weeks after study
medication withdrawal  | Every 12 weeks (counting
from baseline) until
Week 36 or Week 48 b |
| Study Procedure                                                                               |                                                                |                                               |                                                                                     |
| Clinical Laboratory Tests                                                                            |                                                                |                                               |                                                                                     |
| TSH c                                                                                     | X                                                              | X                                             |                                                                                     |
| Hematology/biochemistry d                                                                 | X                                                              | X                                             | X                                                                                   |
| Local urinalysis e                                                                        | X                                                              | X                                             | X                                                                                   |
| Pregnancy test f                                                                          | X                                                              | X                                             | X                                                                                   |
| Efficacy Assessments                                                                                 |                                                                |                                               |                                                                                     |
| HCV RNA quantification                                                                               | X                                                              | X                                             | X                                                                                   |
| Viral sequencing g                                                                        | X                                                              | X                                             | X                                                                                   |
| Other Safety Assessments                                                                             |                                                                |                                               |                                                                                     |
| Physical examination                                                                                 | X                                                              | X                                             | X                                                                                   |
| Vital signs                                                                                          | X                                                              | X                                             | X                                                                                   |
| Patient reported outcomes (PRO)                                                                      |                                                                |                                               |                                                                                     |
| Hepatitis C Symptom & Impact Questionnaire (HCV-SIQ) h                                    | X                                                              | X                                             | X                                                                                   |
| Fatigue (Fatigue severity scale [FSS]) h                                                  | X                                                              |                                               | X                                                                                   |
| Productivity (Work Productivity and Activity Impairment [WPAI]) h                         | X                                                              |                                               | X                                                                                   |
| Depressive symptom severity (Center for Epidemiologic Studies Depression Scale [CES-D]) h | X                                                              |                                               | X                                                                                   |
| Health status (EuroQol 5-dimension questionnaire [EQ-5D]) h                               | X                                                              |                                               | X                                                                                   |
| Ongoing Subject Review                                                                               |                                                                |                                               |                                                                                     |
| Concomitant therapy                                                                                  | X                                                              | X                                             | X                                                                                   |
| Observe/interview for (serious) adverse eventsi                                                      | X                                                              | X                                             | X                                                                                   |

## Footnotes

a Duration of follow-up after early withdrawal will depend on the planned duration of treatment (see Section 3.1):

- subjects who prematurely discontinue all study medication before Week 8 will be followed until Week 36.
- subjects who would have qualified for a total treatment duration of 12 weeks but prematurely discontinued after Week 8 will be followed until Week 36.
- subjects who would have qualified for total treatment duration of 24 weeks but prematurely discontinued after Week 8 will be followed until Week 48.
- subjects who discontinue treatment because they meet a virologic stopping rule at Week 4 or Week 12 will be followed until Week 36.
- subjects who discontinue treatment due to viral breakthrough will be followed until 4 weeks after withdrawal (i.e., they will come back for visits at time of discontinuation and 4 weeks after study medication withdrawal)

- b The first scheduled visit (every 12 weeks from baseline) after study medication withdrawal will not be performed if it coincides (with a time window of  $\pm 7$  calendar days) with the Week 4 visit after study medication withdrawal. In such a case, every effort should be made to ensure that for subsequent visits the schedule every 12 weeks from baseline is adhered to.
- c Free thyroxine (T4) and free triiodothyronine (T3) will be assessed if TSH is abnormal.
- d The biochemistry sample at 12-weekly intervals (counting from baseline) must be taken after fasting for at least 10 hours. It is recommended that biochemistry samples at all other time points also be taken after fasting for at least 10h. The homeostasis model assessment for insulin resistance (HOMA IR) index will be derived from insulin and glucose (fasted) test results at 12-weekly intervals (counting from baseline).
- e Urinalysis performed locally by dipstick. If there are clinically relevant abnormalities in the investigator's opinion, further urinalysis should be done locally (e.g., sediment analysis including RBC, WBC, casts). Clinically relevant findings from local urinalysis will be reported as AEs.
- f Urine test for women of childbearing potential. Extra pregnancy test kits will be given if more than 4 weeks between two consecutive study visits to perform a pregnancy test at home.
- g Sequencing of the HCV NS3/4A region will be done at the discretion of the Study Responsible Scientist.
- h PRO scales should be completed prior to any other study-related activity at each visit.
- i From signing the ICF until 4 weeks after last study medication intake. Thereafter, only AEs considered related to TMC435 will be reported. SAEs will be reported until 30 days after last study-related procedure.

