All subjects will start treatment at baseline (Day 1) and will receive triple therapy consisting of TMC435 plus PegIFN $\alpha$ -2a and RBV for 12 weeks. Total anti-HCV treatment duration will be response-guided based on HCV RNA levels at Week 2, Week 4, and Week 8 as follows:

- Subjects will qualify for a total treatment duration of only 12 weeks (ie all anti-HCV treatment is discontinued after week 12) if the following criteria are met: if HCV RNA value is
  - < 25 IU/mL (detectable or undetectable) at Week 2,  
AND
  - < 25 IU/mL undetectable at Week 4,  
AND
  - < 25 IU/mL undetectable at Week 8.
- if HCV RNA is above the threshold defined above at any of the 3 time points, subjects will stop TMC435 treatment at Week 12 and will continue PegIFN $\alpha$ -2a and RBV until Week 24.

The above treatment continuation criteria will at all times be overruled if a subject meets any of the virologic stopping criteria. Subjects meeting any of the following criteria will be required to discontinue all treatment:

- Week 4: HCV RNA  $\geq$  25 IU/mL
- Week 12: HCV RNA  $\geq$  25 IU/mL OR < 25 IU/mL detectable
- a confirmed increase of > 1 log10 IU/mL in HCV RNA level from the lowest level reached, or a confirmed HCV RNA level of > 100 IU/mL in subjects whose HCV RNA level had previously been < 25 IU/mL while on study drugs.

The study will be conducted in 3 phases: a screening phase of maximum 6 weeks, a treatment phase extending from Day 1 (baseline) up to 12 or 24 weeks depending on the response to treatment, and a posttreatment follow-up period of 24 weeks after the subject's last planned dose of study drug. The duration of the subject's participation (excluding screening phase) will vary between 36 weeks and 48 weeks, depending on the response to treatment. The study will be considered completed with the last visit of the last subject.

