| SVR24              | 
sustained virologic response 24 weeks after planned end of treatment
 
Subjects are considered to have reached SVR24 if both conditions below are met:
 
1) at the actual end of treatment
 

• HCV RNA levels < 25 IU/mL undetectable,

 
AND
 
2) at the time point of SVR24 (i.e., 24 weeks after the planned EOT)
 

• HCV RNA levels < 25 IU/mL undetectable.

 |
| Triple therapy     | Treatment for HCV infection consisting of a direct-acting anti-viral agent (DAA) plus PegIFN/RBV                                                                                                                                                                                                                                                                                                                                                                                             |
| viral breakthrough | Confirmed increase of > 1 log 10 IU/mL in HCV RNA level from the lowest level reached, or a confirmed HCV RNA level of > 100 IU/mL in subjects whose HCV RNA levels had previously been below the limit of quantification (< 25 IU/mL detectable) or undetectable (< 25 IU/mL undetectable) while on study treatment.                                                                                                                                                             |
| W2VR               | HCV RNA < 25 IU/mL (detectable or undetectable) measured 2 weeks after start of treatment.                                                                                                                                                                                                                                                                                                                                                                                                   |

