  - < 25 IU/mL undetectable at Week 8.
- if HCV RNA is above the threshold defined above at any of the 3 time points, subjects will continue PegIFN $\alpha$ -2a and RBV until Week 24.

A diagram of the study design is provided in Figure 1.

Regardless of treatment duration, endpoint to evaluate efficacy will be SVR12.

The treatment continuation criteria will at all times be overruled if a subject meets any of the virologic stopping criteria outlined below. Subjects meeting any of the following criteria will be required to discontinue all treatment:

- Week 4: HCV RNA  $\geq$  25 IU/mL
- Week 12: HCV RNA  $\geq$  25 IU/mL OR < 25 IU/mL detectable
- a confirmed increase of  $> 1 \log_{10}$  IU/mL in HCV RNA level from the lowest level reached, or a confirmed HCV RNA level of  $> 100$  IU/mL in subjects whose HCV RNA level had previously been  $< 25$  IU/mL while on study drugs.

Detectable HCV RNA after previous undetectability should be confirmed by a confirmatory HCV RNA measurement within 2 weeks after receipt of the detectable HCV RNA value. Treatment should only be discontinued after HCV RNA detectability is confirmed (see Section 6.3, Virologic Stopping Criteria for further details).

HCV RNA will be measured centrally and the results will be communicated to the investigational sites. It will be the investigator's responsibility to take the necessary actions regarding the discontinuation of therapy in case a virologic stopping rule has been met.

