**Figure 1: Schematic Overview of the Study**

**All subjects:** 12 weeks of triple therapya; stop all therapy after Week 12 if  
HCV RNA < 25 IU/mL (detectable or undetectable) at Week 2 AND  
< 25 IU/mL undetectable at Week 4 AND  
< 25 IU/mL undetectable at Week 8;  
otherwise continue treatment in Extension

[figure not shown]**Treatment Extension**

If HCV RNA at Week 2, 4 and 8 does not meet the above-outlined criteria for treatment stop at Week 12, the subject should continue PegIFN/RBV until Week 24a

[figure not shown]

a unless a virologic stopping rule is met, see Section 6.3, Virologic Stopping Criteria for further details

b primary endpoint

c secondary endpoint

TMC435 will be taken as oral capsules of 150 mg. PegIFN $\alpha$ -2a and RBV will be given as Pegasys and Copegus (see Section 6.2, Timing of Dosing for further details). Pegasys and Copegus will be administered according to the manufacturer's prescribing information. Pegasys (180  $\mu$ g once weekly) will be administered as weekly subcutaneous (SC) injections of 0.5 mL. The total daily dose of Copegus is weight-dependent. If body weight is < 75 kg, the total daily dose is 1000 mg, administered as 400 mg (2 tablets of 200 mg, morning intake) and 600 mg (3 tablets of 200 mg, evening intake). If body weight is  $\geq$  75 kg, the total daily dose is 1200 mg, administered as 2 x 600 mg (3 tablets of 200 mg per intake, morning and evening).

The study will be conducted in 3 phases: a screening phase of maximum 6 weeks, a treatment phase extending from Day 1 (baseline) up to 12 or 24 weeks depending on the response to treatment, and a posttreatment follow-up period of 24 weeks after the subject's last planned dose of study drug. The duration of the subject's participation (excluding screening phase) will vary between 36 weeks and 48 weeks, depending on the response to treatment.

Subjects should maintain the study visit schedule during treatment interruptions or after premature treatment discontinuation as outlined in the Time and Events Schedule. Additional unscheduled visits may be performed for safety or tolerability reasons if needed.

Interim analyses will be conducted (refer to Section 11.5, Interim Analyses).

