### 6.3. Virologic Stopping Criteria

Subjects will discontinue medication as soon as possible to avoid continued exposure of subjects to a failing treatment and to limit the risk for evolution of resistant HCV variants.

Subjects meeting any of the following criteria will be required to discontinue all treatment:

- Week 4: HCV RNA  $\geq$  25 IU/mL
- Week 12: HCV RNA  $\geq$  25 IU/mL OR < 25 IU/mL detectable
- a confirmed increase of > 1 log10 IU/mL in HCV RNA level from the lowest level reached, or a confirmed HCV RNA level of > 100 IU/mL in subjects whose HCV RNA level had previously been < 25 IU/mL while on study drugs.

Detectable HCV RNA after previous undetectability should be confirmed by a confirmatory HCV RNA measurement within 2 weeks after receipt of the detectable HCV RNA value. HCV RNA will be measured centrally and the results will be communicated to the investigational sites. It will be the investigator's responsibility to take the necessary actions regarding the discontinuation of therapy in case a virologic stopping criterion has been met.

Virologic stopping criteria overrule treatment continuation criteria at all times. If a stopping rule is met, treatment should be discontinued and a study medication withdrawal visit should be scheduled as soon as possible. For details on the assessments during the withdrawal visit, see Time and Events Schedule - Part 4.

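### Follow-up for everyone who stops before Week 8 ends at Week 36, so subjects already ruled out of the 12-week plan have no sample at their SVR24 time point (Week 48)

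*Protocol*

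**What the plan says.** Footnote a to the Time and Events Schedule, Part 4, opens with a principle: "Duration of follow-up after early withdrawal will depend on the planned duration of treatment (see Section 3.1"). The bullets beneath it set the length of follow-up:

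- Stopping before Week 8: "subjects who prematurely discontinue all study medication before Week 8 will be followed until Week 36". There is no split by plan.
- Stopping after Week 8 on a 12-week plan: Week 36.
- Stopping after Week 8 on a 24-week plan: "subjects who would have qualified for total treatment duration of 24 weeks but prematurely discontinued after Week 8 will be followed until Week 48".
- Stopping under the Week 4 or Week 12 virologic rule: Week 36.
- Stopping for viral breakthrough: 4 weeks after withdrawal.

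The duration rule is in the Synopsis and Sections 3.1 and 6.1. Twelve weeks requires meeting the thresholds at Week 2, Week 4 and Week 8 together. Otherwise, in the Synopsis, "if HCV RNA is above the threshold defined above at any of the 3 time points, subjects will stop TMC435 treatment at Week 12" and the other two drugs go on to Week 24. Section 3.1 has the same rule: "if HCV RNA is above the threshold defined above at any of the 3 time points, subjects will continue" to Week 24.

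The Definition of Terms requires undetectable RNA for SVR24 both at the actual end of treatment and "at the time point of SVR24 (i.e., 24 weeks after the planned EOT"). Section 3.1 describes "a posttreatment follow-up period of 24 weeks after the subject's last planned dose of study drug". Section 9.2.2 lists SVR24 as a major secondary endpoint for all subjects, by assigned duration and by genotype.

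**The concern.** The first bullet does not follow the principle stated directly above it. The second and third bullets do. The 12-week plan can be ruled out at Week 2 or Week 4, well before Week 8, yet the first bullet gives all earlier stoppers the follow-up of a 12-week plan.

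At stake is whether SVR24 can be observed. Take a subject who misses the Week 2 threshold, is undetectable at Week 4, and stops all drugs at Week 6 because of an adverse event. If still undetectable at Week 36, this subject has a known SVR12 and an unknown SVR24, because the schedule provides no Week 48 sample.

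**Working it through.** **Inputs**

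- Planned end of treatment: Week 12 or Week 24 (Sections 3.1 and 6.1).
- SVR time points: planned end of treatment plus 12 or plus 24 weeks (Definition of Terms).
- Last visit for anyone stopping before Week 8: Week 36 (Part 4, footnote a).
- Expected eligible for 12 weeks: 104 of 150 genotype 1 and 52 of 75 genotype 4 (Section 11.2).

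**Step 1. Reproduce the protocol's own figure.** Section 3.1 gives participation of 36 to 48 weeks, excluding screening. 12 + 24 = 36 and 24 + 24 = 48, so the figure is reproduced. It confirms that follow-up is meant to run 24 weeks from the planned end.

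**Step 2. Place the SVR time points.**

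| Plan | SVR12 | SVR24 | Week 36, counted from planned end |
|---|---|---|---|
| 12 weeks | 12 + 12 = Week 24 | 12 + 24 = Week 36 | 36 − 12 = 24 weeks |
| 24 weeks | 24 + 12 = Week 36 | 24 + 24 = Week 48 | 36 − 24 = 12 weeks |

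With a last visit at Week 36, a 24-week subject reaches SVR12 and stops 12 weeks short of SVR24.

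**Step 3. Who can be ruled out of 12 weeks before Week 8?** There are two routes: 25 IU/mL or more at Week 2, or below 25 IU/mL but detectable at Week 4. A value of 25 IU/mL or more at Week 4 is different. Under Section 6.3, "Subjects meeting any of the following criteria will be required to discontinue all treatment", and the Week 4 criterion is one of those listed. These subjects have their own Week 36 bullet and are outside this point.

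**Step 4. For whom is information lost?** SVR24 also needs undetectable RNA at the actual end of treatment. Anyone detectable on stopping has failed SVR24 already, and anyone detectable at Week 36 has visibly failed or relapsed. Only a subject undetectable at both has an open outcome at Week 48.

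**Step 5. How many?** Not expected to qualify for 12 weeks: 150 − 104 = 46 and 75 − 52 = 23, together 69. This includes Week 4 rule stoppers, so it overstates the group at risk. The protocol gives no rate of stopping before Week 8. If 2% to 5% do (assumed), 69 × 0.02 = 1.4 and 69 × 0.05 = 3.5 subjects stop. The nearest figure in the protocol is 1.8% stopping TMC435 for adverse events in the pooled Phase 3 studies (Section 1.2). It covers one drug and one reason only; 69 × 0.018 = 1.2. All these counts come before the two conditions in Step 4. If half of the stoppers met both (also assumed), 1.4 / 2 = 0.7 and 3.5 / 2 = 1.7, hence about 0 to 2. At an assumed 10%, 69 × 0.10 = 6.9 would stop, again before those conditions.

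**Step 6. Weight of one subject.** 1/46 = 2.2 percentage points for genotype 1 and 1/23 = 4.3 for genotype 4. Both are approximate, because 46 and 23 are not the exact sizes of the 24-week groups.

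**The case against.** The strongest reply is that no duration is assigned until Week 8. All subjects start the same 12-week course, and footnote a separates the two plans only after Week 8. A Week 2 miss also does not guarantee 24 weeks, since the Week 4 rule may still end treatment. If everyone held a 12-week plan until Week 8, Week 36 would be the SVR24 time point and nothing would be lost. The protocol nowhere states such a default, however, and it conflicts with a rule under which one miss at any of the three time points removes the 12-week option. If these subjects instead have no assigned duration, they have no place in an endpoint reported for all subjects by assigned duration.

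A second reply is that shorter follow-up for early stoppers is deliberate. Sections 3.1 and 10.1 refer early stoppers to the Part 4 schedule. Section 9.1.4 asks for at least 24 weeks after treatment, which Week 36 satisfies when counted from the actual stop (more than 36 − 8 = 28 weeks). That stands as far as it goes, and it weakens any claim that Section 3.1 is breached outright. It does not supply the Week 48 sample that the SVR24 definition needs. Nor is the Week 36 limit for virologic stoppers a precedent: a subject detectable when treatment ends has already failed SVR24.

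A third reply concerns size, and it stands. The early-stop rate is assumed, 46 and 23 are too large for the group at risk, and many of these slower responders may stop while still detectable.

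**Conclusion.** The inconsistency is real, and it rests on week arithmetic alone. For subjects who missed the Week 2 threshold, or were below 25 IU/mL but detectable at Week 4, and then stopped before Week 8 for a non-virologic reason, SVR24 falls at Week 48 and is not observed.

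Its effect is small: probably about 0 to 2 subjects, resting on the assumed early-stop rate and the assumed share who are undetectable both at stopping and at Week 36. It touches SVR24, a major secondary endpoint, and relapse between Weeks 36 and 48. SVR12 is still observed. The primary endpoint, SVR12 in genotype 1 subjects assigned to 12 weeks, is untouched.

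A reader might infer that the schedule turns all these subjects into non-responders and so biases SVR24 in the 24-week group. The protocol does not support that. Some will have failed SVR24 at the actual end of treatment, and the handling of a missing Week 48 value is left to the statistical analysis plan, which is not shown.

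**What to change.** Reconcile the first bullet of footnote a with the footnote's opening sentence and with the SVR24 definition by splitting it:

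- Subjects who stop before Week 8 with no threshold missed so far: follow-up to Week 36, as now.
- Subjects who stop before Week 8 having already missed the Week 2 or Week 4 threshold, and who did not stop under a virologic stopping rule or for viral breakthrough: follow-up to Week 48, as in the third bullet.

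State in the same place what the planned end of treatment is for each group, so that both SVR time points are defined for everyone.

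The cost is a sentence or two in the footnote and one further 12-weekly visit for a few subjects. The Part 4 column heading already allows for Week 36 or Week 48. No dose, treatment duration or stopping rule changes. Leaving follow-up as it is and dropping these subjects from the SVR24 denominator is not a good substitute: it would condition the analysis on early discontinuation and depart from the intent-to-treat population in Section 11.
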